### Staff outcome measures

#### Working alliance (key workers, therapists)

Staff outcomes and schedule of data collection are presented in Tables 3 and 4. The staff version of the *WAI-12* [68] will be completed by key workers in relation to the service user at the three assessment time points. Items are identical to those of the service user measure but are reworded to reflect the perspective of the staff members. The lead and co-therapists will also complete the WAI in relation to the service user and each family member/FSM at the end of session 3. The WAI has previously been used with key workers and therapists [74–76].

**Table 3 Tab3:** Key Worker Assessment Schedule

Assessment tool		Time point			
		Duration (min)	Baseline	Post-CaFI	3-month follow-up
Referral info. and demographic	Socio-demographic	10	x		
WAI—short form	Working alliance	5	x	x	x
SES	Service engagement	5	x	x	x
Qualitative interview (*n* = 10)	Acceptability and feasibility	30–45			x
Total time burden			20	10	40–55

**Table 4 Tab4:** Therapist assessment schedule

Assessment tool		Time point			
		Duration (min)	Baseline	Post-CaFI	3-month follow-up
Qualitative interview	Acceptability and feasibility	30–45			x
WAI—short form session 3	Therapeutic alliance	5 min complete during session 3			
Total time burden		50 min			

#### Service engagement (key workers)

The *Service Engagement Scale* (SES) [77] is a 14-item self-report measure assessing participants’ engagement with services from a key worker perspective. The measure has four subscales; availability; collaboration; help-seeking; and treatment adherence. The SES has been validated in a psychosis sample, with evidence of good psychometric properties [77].

### Fidelity study

The CaFI fidelity measure comprises a modified version of the subscale of the Cognitive Therapy Scale for Psychosis (CTS-PSY) (Haddock et al. 2001), which has been adapted for this study to account for the presence of two therapists and the relatives. Six items will be used: agenda setting, feedback, understanding, interpersonal effectiveness, collaboration, homework and quality of CBT techniques. The second subscale includes components that map directly onto the CaFI therapy manual along with two additional items from the Family Interventions in Psychosis-Adherence Scale (FIPAS) (Onwumere et al. 2009): reducing criticism and conflict and reducing over-involvement. Fidelity will be assessed by independent ratings of 10 % of randomly selected sessions. Treatment fidelity and quality will also be monitored via discussion of audio-recordings of sessions in supervision.

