**Discussion:**

This innovative response to inequalities in mental healthcare experienced by African-Caribbeans diagnosed with schizophrenia might improve engagement in services, access to evidence-based interventions and clinical outcomes. Successful implementation of CaFI in this group could pave the way for better engagement and provision across marginalised groups and therefore has potentially important implications for commissioning and service delivery in ethnically diverse populations. This study will demonstrate whether the approach is feasible and acceptable and can be implemented with fidelity in different settings.

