#### Therapists and training

Each CaFI session will be delivered by a lead therapist (NHS Agenda for Change Band 7) and a co-therapist (NHS Band 4). Three pairs of therapists (*n* = 6) have been recruited to deliver 300 h of CAFI to 30 families (30 × 10 hourly sessions); equating to 100 h of therapy per therapist over the 12-month intervention period. Therapists have come from a range of professions, including clinical psychology, social work, mental health nursing and occupational therapy. Lead therapists have relevant training and skills in CBT and FI, either directly through their current profession or through advanced training in psychosocial interventions for psychosis. Co-therapists are current mental health support workers or assistant psychologists. Therapists deliver CaFI as part of their current caseload—reflecting our ultimate goal to embed FI within NHS services. To ensure familiarity with our ‘ethos of delivery’, all six therapists have received 2 days of training in cultural competence (delivered by *Just Psychology* [42]) and family working skills (delivered by *Meriden Family Programme* [48]). Key components of therapists’ training included the following: (i) core competences to work effectively with families experiencing schizophrenia and psychosis [49]; (ii) current legislation and how it relates to clinical practice (such as The Equality Act, 2010) [50], and NHS Knowledge Skills Framework requirements [51]; (iii) cultural awareness and family work practice (for example, the potential impact of culture and family experience on delivery of evidence-based FI components and cultural diversity within African-Caribbean communities); (iv) relationship between racism, discrimination, adversity and mental health; and (v) the significance of power and prejudice in building trusting therapeutic relationships. Therapists also received half-day training in the CaFI manual facilitated by the research team [PI, RA and clinical supervisor] to engender confidence in delivering the sessions. Therapists will receive bi-weekly hourly supervision from an experienced clinical psychologist on the research team. To share good practice and highlight common issues within sessions, there will also be group supervision sessions. The frequency of these will be agreed with the therapists and depend on need.

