#### Manual content

The CaFI intervention includes five key components:
*Engagement and assessment [two sessions]*
In the development phase, participants stressed the importance of taking time to build trust given the history of negative relationships between African-Caribbeans and statutory mental health services. Accordingly, in these initial sessions, the emphasis will be on trust-building and engagement, developing a positive therapeutic relationship, and establishing working therapeutic alliance between family members. Therapists will undertake a thorough assessment of the family; identifying strengths and resources as well as a formulation of needs. Additionally, explanation of the intervention is provided (including proposed structure and purpose and potential benefits to the family), problems identified and prioritised based on the family’s wishes and formulation, realistic SMART (specific, measurable, attainable, relevant, timely) goals and expectations for future session set.
*Shared learning [two sessions]*
‘*Shared learning*’ is a collaborative approach to psycho-education designed to facilitate engagement and alliance. This approach allows the therapist, relatives and service user to learn from each other’s experiences and acquire knowledge that will lead to more beneficial ways of managing difficulties related to schizophrenia and psychosis in the family. This is an important aspect of cultural-adaptation for this ethnic group; particularly in terms of addressing illness beliefs and explanatory models. In conjunction with initial assessment, these sessions lay the groundwork for other components of the intervention and behaviour change.
*Communication [two sessions]*

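### The random 10% fidelity sample leaves coverage by setting to chance, and the first fidelity subscale is announced with six items but lists seven

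*Protocol article*

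**What the plan says.** The Fidelity study section sets both the sampling rule and the instrument. On sampling: "Fidelity will be assessed by independent ratings of 10 % of randomly selected sessions". The abstract repeats the 10% figure. Neither place mentions strata for therapist pair, component or setting. The section adds that recordings will also be discussed in supervision.

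On the instrument, the first subscale is adapted from an existing cognitive therapy scale: "Six items will be used: agenda setting, feedback, understanding, interpersonal effectiveness, collaboration, homework and quality of CBT techniques". The second subscale follows the content of the therapy manual and adds two items from a family-intervention adherence scale.

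The size of the sampling frame comes from Therapists and training: "Three pairs of therapists (*n* = 6) have been recruited" to "deliver 300 h of CAFI to 30 families (30 × 10 hourly sessions"). Manual content says "The CaFI intervention includes five key components" and allots two sessions to each. Participants and recruitment procedures names three settings: acute wards, rehabilitation units and the community. The closing paragraph of the abstract says the study will show whether the approach is feasible and acceptable and "can be implemented with fidelity in different settings".

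**The concern.** Fidelity across settings is one of the few things the article says the study will demonstrate. The sampling rule, as written, does nothing to secure it: how many rated sessions fall in each setting depends on the draw and on a case mix that the article does not fix. A setting with few families could end up with no rated sessions or only one or two.

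The draw also matters for content. Sessions are tied to particular manual components, and the second subscale is built on those components. Which sessions are drawn therefore decides on what content each pair is rated.

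The item count is a separate matter. One sentence gives a number and a list that disagree, so a rater or analyst cannot tell from the article whether the first subscale has six items or seven.

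**Working it through.** **Inputs.** From Therapists and training: 30 families, 10 sessions each, three therapist pairs. From Manual content: five components of two sessions each. From Fidelity study: 10%, random. From Participants and recruitment procedures: three settings. Assumed, because the article does not say: a simple random draw without replacement, equal caseloads per pair, all 300 sessions delivered and recorded, and the number of families per setting.

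**The plan's own figures.** 30 × 10 = 300 sessions. Both members of a pair attend each session, so 300 / 3 = 100 h per therapist. This agrees with "equating to 100 h of therapy per therapist over the 12-month intervention period". Five components × 2 sessions = 10 sessions. The fidelity sample is 0.10 × 300 = 30 sessions.

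**Formula.** For a group of K sessions, the chance that none is drawn is C(300 − K, 30) / C(300, 30).

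**Pairs and components taken singly**
- A component has K = 60. P(a given component unrated) = C(240,30)/C(300,30) = 0.0008. P(any of the five unrated) = 0.004.
- A pair has K = 100. P(a given pair unrated) = C(200,30)/C(300,30) ≈ 0.000002, so for any of three it is effectively zero.

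**Settings.** The split is assumed; the same hypergeometric distribution gives the chance of two or fewer.

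| Families in one setting | Sessions K | Expected rated | P(none rated) | P(two or fewer rated) |
|---|---|---|---|---|
| 3 | 30 | 3 | 0.036 | 0.40 |
| 5 | 50 | 5 | 0.003 | 0.09 |
| 10 | 100 | 10 | about 0.000002 | below 0.001 |

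**Pair-by-component cells.** 3 × 5 = 15 cells with 300 / 15 = 20 sessions each, so 30 / 15 = 2 ratings per cell on average.
- P(a given cell unrated) = C(280,30)/C(300,30) = 0.113.
- Expected unrated cells = 15 × 0.113 = 1.69.
- P(at least one unrated), by exact inclusion-exclusion = 0.883. Simulation with 200,000 draws gives 0.884, and 0.55 for two or more.
- With unequal caseloads (assumed), the chance of at least one is 0.90 for 120/100/80 sessions and 0.95 for 150/90/60. With fewer sessions delivered (assumed), it is 0.977 for 24 rated of 240 and 0.994 for 21 of 210.

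**After stratifying.** Two sessions drawn from each of 15 cells is again 30 ratings, and no cell is empty provided each has at least two recorded sessions. Adding setting gives 15 × 3 = 45 cells, more than 30 ratings can fill, so setting can be balanced only at the margin.

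**Item count.** Named: agenda setting (1), feedback (2), understanding (3), interpersonal effectiveness (4), collaboration (5), homework (6), quality of CBT techniques (7). Stated: six.

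**The case against.** The best reply is that simple random sampling is a valid choice. It is unbiased for overall fidelity, it covers every pair and every component almost surely, and the article announces no analysis by pair-by-component cell. The 88% is thus the chance of missing a target the study never set. For settings, the level the abstract does name, a wholly unrated setting is improbable unless that setting is small. A condensed article may also leave the selection procedure to the full protocol, and a random draw does not exclude strata. All of this stands. It reduces the sampling point to an inexpensive improvement. What remains is that the rule as printed leaves setting coverage to chance while the abstract makes a claim about settings. Discussing recordings in supervision is not independent rating and does not fill that gap.

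Three stronger readings are tempting, and the documents support none of them:
- *That the study cannot show fidelity in different settings.* A sample that misses some pair-by-component cells can still contain rated sessions from every setting.
- *That families without a rated session reveal a flaw.* Any given family has a 34% chance of none, but every 10% sample leaves many families unrated, and no rating per family is promised.
- *That the six-or-seven slip makes fidelity scores non-reproducible.* The article states no total, mean or threshold, and the rating form is not shown, so no effect on a score can be derived.

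**Conclusion.** The point holds as a low-cost design improvement together with one internal contradiction.

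On sampling, the overall fidelity estimate is sound. The weakness is uncontrolled coverage by setting, and it matters only if a setting is small: at 3 families there is a 0.04 chance of no rated session and a 0.40 chance of two or fewer; at 10 families the risk is negligible. The 88% chance of an empty pair-by-component cell is a secondary argument for stratifying. These figures rest on a simple random draw of 30 from 300, with equal caseloads and full delivery for the cell figure and an assumed split for the setting figures. Unequal caseloads or lost sessions raise the cell figure.

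On the instrument, the contradiction between the stated and listed number of items is certain and needs no assumption. The article does not show which of the two is right.

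**What to change.** Draw the same number of sessions by stratified random sampling on therapist pair and manual component, about two per cell where recordings allow. Within that, balance acute, rehabilitation and community at the margin as far as the case mix permits. If sampling fractions differ between strata, weight the overall fidelity estimate accordingly.

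Reconcile the stated number of items in the first subscale with the items listed, and do so before rating starts.

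The cost is small: no extra ratings, but a running list of sessions by pair, component and setting must be kept. Exact balance over settings may be out of reach, because 45 cells exceed 30 ratings and a pair may work mainly in one setting. The item correction is a change to one number or to the list.

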### Qualitative data

Qualitative interviews of all consenting participants will be conducted post-intervention (within the 3-month follow-up period) to assess the acceptability of the intervention to service users, biological families/FSMs and therapists. In addition, we shall interview a sample of key workers (*n* = 10) purposively selected to achieve-variation in gender, profession, length of experience, clinical setting, participants’ retention in CaFI (i.e. those who completed the sessions and those who withdrew) and familial relationship type (biological family member/FSM). Data will be collected using topic guides specifically designed to explore participants’ perspectives on different aspects of the study such as the following: (i) taking part in research; (ii) content and delivery of sessions; (iii) usefulness, cultural-appropriateness and accessibility of intervention and materials; (iv) barriers/facilitators to implementation; (vi) training/supervision; (vii) personal benefits; (viii) delivery via FSMs and therapists. Inclusion of open-ended questions in a semi-structured interview format will enable us to explore aspects of the intervention that participants particularly liked/disliked and areas which they think should have been improved.

Participants (service users and biological family members/FSMs) who withdraw from the intervention early will be asked to complete a withdrawal form and the above qualitative interview, with redundant items removed. Additional questions will be asked about why they left early and what could have been done differently to facilitate retention.

### Data analysis

*Quantitative analyses* of demographic information and quantitative elements of the questionnaires will be presented using descriptive statistics [78]. We shall also present descriptive statistics on recruitment, consent, adherence and attrition, including exploratory analysis of factors affecting adherence and attrition'. We shall examine the characteristics of the various outcome measures to consider which might be most appropriate in a future trial and estimate variability to inform sample size calculation. We are aware of the problem of loss to follow-up in mental health trials. We shall prepare for this in a future trial by examining outcomes at points of departure from the trial. Quantitative data will be analysed using STATA 14 [79].

*Qualitative data* will be digitally-recorded, transcribed, checked for accuracy and analysed using thematic analysis [80]. NVivo-10 [81] will support data management and analysis. Thematic analysis is a useful and flexible method for identifying and describing themes (or patterns of meaning) from rich qualitative data [80]. The themes will be derived inductively to an extent but coding and analysis across interviews will be guided by study objectives. Coding will therefore be an iterative process, developed over time by moving back and forth through the following phases of analysis to ensure themes are developed in a methodologically rigorous way [80]: data familiarisation, searching for themes; reviewing themes; and defining and naming themes.

## Discussion

Despite decades of research and major Department of Health investment aimed at ‘Delivering Race Equality’ in mental health [15], NICE concluded that the care and treatment of African-Caribbeans diagnosed with schizophrenia remains in crisis [5]. Service responses are inconsistent and often ineffective. NICE guidance [5] highlights an urgent need to develop culturally appropriate, evidence-based interventions for African-Caribbeans because, compared with other studied groups, evidence suggests they experience significantly higher levels of morbidity, inferior access to care and worse outcomes [10, 14]. Proactive, recovery-based, family-centred approaches improve risk management and outcomes by identifying early warning signs and addressing them [82].

In response to this, we have developed a potentially ground-breaking innovation to meet the specific needs of African-Caribbean people thus improving access and reducing inequity in clinical outcomes for members of this ethnic group. Not only have we culturally-adapted an existing well-established clinical FI [83], but we have also engaged directly with local African-Caribbean stakeholder communities and successfully recruited ‘proxy family’ members to enable service users, who might otherwise be excluded due to lack of family contacts, to receive FI. In so doing, we have overcome one of the greatest challenges to developing and testing our intervention, namely engaging with a so called ‘hard-to-reach’ community with a long history of mistrust of statutory mental health services and high levels of community stigma. Engaging community members in delivering the intervention potentially addresses an important access barrier for African-Caribbeans who are especially likely to experience family disruption [29]. Other important and novel aspects of the study include testing the intervention in both hospital (acute and rehabilitation wards) and community settings and making it available to individuals on CTOs. We shall test the feasibility of implementing the evaluation and evaluating its acceptability among African-Caribbean service users, their families and service stakeholders.

Successful implementation of CaFI will facilitate and improve engagement in services for African-Caribbean people with schizophrenia diagnoses (ICD F20-29), thus improving access to a range of evidence-based interventions designed to improve patient- and service-led outcomes. Successful implementation of CaFI in the African-Caribbean community, with its innovative solution to therapeutic engagement of disrupted family units and people living with severe mental illness, offers a means of improving access to evidence-based care and clinical and life outcomes for other socially excluded and marginalised communities. This is especially important in the current climate of refugee and asylum-seeker migration, which means that the landscape of delivering mental health care for minority populations is changing rapidly. It is therefore increasingly imperative that new solutions are found to tackle persistent, ethnically-based inequities in mental health care, which are likely to represent ongoing challenges for policy makers, commissioners and service providers.

## Abbreviations

BME, Black and Minority Ethnic; CaFI, Culturally-adapted Family Intervention; CaKAP, Culturally-adapted Knowledge about Psychosis; CRN, Clinical Research Network; CSOs, Clinical Studies Officers; CTOs, Community Treatment Orders; CTS-PSY, Cognitive Therapy Scale for Psychosis; FI, Family Intervention; FIPAS, Family Interventions in Psychosis-Adherence Scale; FSM, Family Support Members; GHQ-12, General Health Questionnaire; GPs, General Practitioners; HS&DR, Health Service and Delivery Research; IPQ, Illness Perception Questionnaire; KAP, Knowledge about Psychosis; KAPI, Knowledge about Psychosis Interview; KASI, Knowledge about Schizophrenia Interview; MMHSCT, Manchester Mental Health and Social Care Trust; NICE, National Institute of Health and Care Excellence; NIHR, National Institute for Health Research; NRES, National Research Ethics Service; PANSS, Positive and Negative Syndrome Scale; PCS, Perceived Criticism Scale; PIS, Participant Information Sheet; PPI, Patient and Public Involvement; PSP, Personal and Social Performance Scale; QALYs, quality-adjusted life years; RAG, Research Advisory Group; RAs, research assistants; RCT, Randomised Controlled Trials; SES, Service Engagement Scale; SMART, Specific, Measurable, Attainable, Relevant, Timely; SMI, severe mental illness; START, Systematic Techniques for Assisting Recruitment to Trials; WAI, Working Alliance Inventory
